***Hypotheses:***

1. Exposure to the video will elicit favorable reactions from patients as evidenced by their paying attention to the video and other positive responses, such as smiling.
2. Exposure to the video will contribute to a greater proportion of HIV-positive persons currently on treatment who adhere to their HIV medication regimen.
3. Exposure to the video will contribute to earlier initiation of antiretroviral therapy (ART) among treatment naïve HIV-positive persons.
4. Exposure to the video will increase retention in care among HIV-positive persons in care.
5. Exposure to the video will decrease sexually transmitted disease (STD) incidence among HIV-positive persons in care.

***General approach:*** The approach will be developmental. Both the observation and the review of de-identified patient medical data are meant to identify areas of the video that need to be refined or improved to optimize its effectiveness.

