***Sampling, including sample size and statistical power:***

The sample for the systematic observation will be a convenience sample of all patients who are present in the waiting room during the 1 day of observation at each facility. A maximum of 8 observational assessments will be done at each facility (32 total assessments). Each observational assessment will consist of systematic observation of all waiting room patients during one video cycle and systematic observation of four waiting room patients during the next video cycle. The four patients will be chosen randomly among patients who have a clear view of the video with the intent of obtaining diversity regarding age, gender, and race/ethnicity. See Appendix 2 for the observation protocol for additional details. The unit of analysis will be the individual patients. We do not expect to revise the sampling estimates for the study.

The sample for the patient medical record data will include all HIV-positive clinic patients and their records during the historical comparison period and the intervention period. Simplified sample size calculations were performed for rejecting the null hypothesis of equality in the proportions of successes for a specific outcome, assuming equal numbers of patients in each period. These calculations correspond to an analysis using Fisher’s exact test with a two-sided significance level of α = 5%.

For the primary outcome of medication adherence (achieving viral load suppression at 6 months), if the true proportions of successes for the two periods are 70% and 77% (historical comparison to intervention, 7% absolute improvement, 10% relative improvement), then sample sizes of 650 patients prescribed ART per period will be required to have 80% power to reject this null hypothesis. Allowing for an annual attrition rate of 25%, then sample sizes of 1157 patients per period will be required to have 80% power to reject this null hypothesis.

For the secondary outcome of retention in care at 3-7 months of follow-up, if the true proportions of successes for the two periods are 75% and 82% (historical comparison to intervention, 7% absolute improvement, 9% relative improvement), then sample sizes of 566 patients per period will be required to have 80% power to reject this null hypothesis. Allowing for an annual attrition rate of 25%, then sample sizes of 1008 patients per period will be required to have 80% power to reject this null hypothesis.

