***C. VARIABLES/INTERVENTIONS***

***Variables:***

Patient medical data will be collected from the EMR, de-identified at the clinic using a computer-generated algorithm, and placed on an encrypted USB drive before mailing to the data manager for analysis. The following patient medical data will be collected:

- unique project ID number,
- gender,
- gender identity (if available),
- race/ethnicity,
- age,
- HIV risk factor,
- clinic visit dates,
- no-shows for scheduled outpatient visits,
- case management center visit dates (for Miami site only),
- date of HIV diagnosis,
- date of ART initiation,
- ART regimens,
- CD4 counts and test dates,
- viral loads and test dates,
- STD lab results and test dates

Observation assessments will include all patients in the waiting room, and more detailed observation of select patients.

Observation variables for the entire waiting room:

- Number of patients by apparent age
- Number of patients by apparent race/ethnicity
- Number of patients by apparent gender
- Number of patients who have a clear view of a video monitor
- Number of patients in the waiting room that the observer can see (to measure engagement with video)
- Number of patients in the waiting room who were present for the previous cycle
- General observations about engagement with each video segment for all patients for one cycle of the video

Observation variables for up to 4 select patients and up to 4 replacement patients:

- Apparent age of each patient
- Apparent race/ethnicity of each patient
- Apparent gender of each patient
- The duration of engagement with video for each video segment
- Reactions and watching behaviors of patient during each video segment
- General comments relative to engagement of the patients for one cycle of the video

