Analysis of patient medical data: For analytical purposes index visits are defined as a patient’s first HIV care clinic visit during a beta-test period (i.e., the historical comparison period or the intervention period). Patients may have index visits in both time periods. The index visit in each period will be time zero. Initiation of ART will be defined as the proportion of treatment-naïve patients (i.e., no previous record of an ART prescription) who are prescribed ART (as per the current treatment guidelines) on their index visit. Medication adherence will be defined as the proportion of patients prescribed ART who achieve viral load suppression (<50 copies/mL) at least 40 days after their index visit. Retention in HIV medical care is defined as the proportion of patients who are retained in care at 3 to 7 months of follow-up from their index visit. Partner protection will be assessed using a proxy measure—incident STDs. Incident STD is defined as the proportion of patients who do not have an incident STD as a function of time since their index visit. Incident STD is defined as a microbiologically confirmed STD diagnoses noted in patients’ electronic medical records (EMRs). Kaplan-Meier methods will be used to estimate the proportion of patients who achieve intervention outcomes. The analyses may be adjusted for patient-level covariates, such as age, race, gender, baseline viral load suppression, and baseline STD, as well as the three beta-test treatment facilities.

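### The partner-protection outcome requires no STD test, so a rise in visits or testing would raise detected STDs and bias Hypothesis 5 against the video

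*Protocol*

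**What the plan says.** Section III.D of the Protocol (Data analysis plan, patient medical data) uses incident STD as a proxy for partner protection and defines the term in two consecutive sentences. The first reads "Incident STD is defined as the proportion of patients who do not have an incident STD", followed over time from the index visit. The second reads "Incident STD is defined as a microbiologically confirmed STD diagnoses noted in" the patients' electronic records. For the estimate it says "Kaplan-Meier methods will be used to estimate the proportion of patients who achieve intervention outcomes". It does not say when a patient's follow-up for STDs ends. Neither testing nor visit frequency is among the covariates it names for optional adjustment.

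The Hypotheses section (II) predicts "Exposure to the video will increase retention in care among HIV-positive persons in care" and "Exposure to the video will decrease sexually transmitted disease (STD) incidence among HIV-positive persons in care". The list of variables in III.C includes "STD lab results and test dates". The sampling section (III.B) says that the study is not powered for STD incidence.

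The bias section (III.D) lists tests not done at every visit, and anatomical sites left untested, as sources of bias. It says that attrition will be adjusted for analytically.

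**The concern.** Under this definition, an STD can be found only if the patient attends, is tested, tests positive and has the result recorded. A patient who attends but is never tested cannot have an event and, on the plain wording, stays in the STD-free proportion. Detection therefore depends on how often patients are seen and tested, and Hypothesis 4 says that the video should increase how often they are seen. A second route is plausible but not stated: the Protocol summary says the video encourages patients to raise these topics with their providers, which could prompt testing even at an unchanged number of visits.

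Success on retention could thus show up as apparent failure on partner protection. The outcome is unpowered, but it stands in Objective 2, in Hypothesis 5 and in the outcome list. The general approach also uses the medical data to find parts of the video to refine. An artefactual rise in STDs could misdirect revision of the partner-protection content.

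The first definition is also worded backwards, since it gives the name of the event to the proportion without it.

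**Working it through.** **Inputs from the Protocol.** Retention of 75% (historical) and 82% (intervention), from the sampling section. There is no sample size, rate or power for the STD outcome to reproduce. The nearest figure is the retention sample size of 566 per period. The usual two-proportion formula gives 540 without and 568 with continuity correction. The second matches the stated figure closely, so 75% and 82% are the plan's working values.

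**Assumed, not in the documents.** True STD incidence of 10% over ten months in both periods; visits at 3, 6 and 9 months; each visit attended with probability 0.75 or 0.82 (the retention figures used as attendance); a test at 50% of attended visits, or 60% in the intervention period in a second scenario.

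**Step 1: detection only in retained patients.** Detected proportion = incidence × retention × testing.
- Historical: 0.10 × 0.75 × 0.50 = 3.75%. Intervention: 0.10 × 0.82 × 0.50 = 4.10%.
- Ratio = 0.82/0.75 = 1.093, whatever the incidence or the common testing rate. A true fall of 1 − 0.75/0.82 = 8.5% would be hidden.
- On the outcome's own scale this is 96.25% against 95.90% STD-free, or 0.35 points.
- With testing of 60% in the intervention period: (0.82 × 0.60)/(0.75 × 0.50) = 1.312.

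**Step 2: follow-up over time, everyone kept to period end.** With a monthly rate of −ln(0.9)/10, new infections are 0.03111 of the cohort by month 3, 0.03015 in months 3 to 6 and 0.02921 in months 6 to 9. Let q = attendance × testing per visit. Then detected = 0.03111 × [1 − (1 − q)³] + 0.03015 × [1 − (1 − q)²] + 0.02921 × q.
- q = 0.375 (historical): 0.02352 + 0.01837 + 0.01095 = 0.05284.
- q = 0.410 (attendance rises): 0.02472 + 0.01965 + 0.01198 = 0.05635; ratio 1.066.
- q = 0.492 (attendance and testing rise): 0.02703 + 0.02237 + 0.01437 = 0.06377; ratio 1.207.

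**Step 3: positives per patient tested.** The proportion tested at least once is 1 − (1 − q)³ = 0.7559, 0.7946 and 0.8689. Positives per patient tested are 0.05284/0.7559 = 0.0699, 0.05635/0.7946 = 0.0709 and 0.06377/0.8689 = 0.0734. The ratios are 1.01 and 1.05.

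**Step 4: other censoring rules.** Simulation of the same model gives these ratios (intervention/historical) with no true change in incidence:

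| Follow-up ends at | Testing 50% in both periods | Testing 50%, then 60% |
| --- | --- | --- |
| Period end | 1.06 to 1.07 | 1.19 to 1.21 |
| Last visit | 1.01 to 1.04 | 1.12 to 1.15 |
| Last test | 0.97 to 0.995 | 0.90 to 0.95 |
| Interval-censored between test dates | 1.00 | 0.99 |

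The ranges cover repeated runs and largely reflect simulation error. With 40,000 patients per period there are about 0.053 × 40,000 = 2,120 historical events at period end, so one ratio has a standard error of about 0.03. Exact enumeration of the model gives 1.01 for last visit with equal testing, and 0.98 and 0.95 for last test.

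Censoring at the last test overshoots because patients still at risk at a late test carry infections accumulated since their previous test. Sparser testing therefore inflates the historical estimate.

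**The case against.** The strongest reply has five parts.

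- **The bias section already concedes incomplete testing** and promises adjustment for attrition. This is true, and it would be wrong to say that the Protocol mentions only anatomical sites. But it gives no direction, draws no link to Hypothesis 4 and offers no remedy for patients who return and are not tested.
- **Censoring detail may sit in an SAP that is not at hand.** This stands, so the missing rule is not a fault by itself. But the Protocol fixes a definition that requires no test. Under period-end censoring the bias remains. Under last-visit censoring it is close to nil if testing per visit is unchanged, and remains if testing rises.
- **The outcome is an unpowered proxy.** That lowers the stakes, but low power is imprecision and does not remove a systematic shift.
- **The reversed sentence is an editorial slip.** Largely so: it describes a survival function, the next sentence defines the event, and the outcome list gives the intended direction.
- **Limiting the analysis to tested follow-up has a bias of its own.** This stands and shapes the fix.

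A reader might infer that a 9.3% bias is built in, or that the final estimate for Hypothesis 5 must err against the video. The documents support neither. The 9.3% needs all detection to occur in patients who meet the retention definition, yet others can be tested before month 3 or after month 7. The differential arises only if visits or testing do rise. The bias section also says that the historical comparison tends to exaggerate the effect, which pulls the other way, so the net sign is unknown.

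**Conclusion.** The concern holds in conditional form. As worded, the outcome counts untested follow-up as STD-free unless follow-up is limited to tested time. A rise in visits, which Hypothesis 4 predicts, or in testing pushes detected STDs up and biases Hypothesis 5 against the video.

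Under the assumptions listed, the spurious ratio is about 1.01 to 1.07 from attendance alone and about 1.12 to 1.21 if testing per visit also rises from 50% to 60%. The figure of 1.093 is an upper illustration under equal testing. No document supports a particular STD incidence, testing rate or rise in testing, so these figures show direction and order of size and are not estimates. The primary outcome, viral suppression, is not affected. The point bears on the interpretation of a secondary, unpowered outcome and is worth correcting because the correction is cheap.

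**What to change.** In the data analysis plan (III.D):

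1. Replace the reversed sentence. Define the event as a first microbiologically confirmed STD after the index visit, and the outcome as the STD-free proportion over time since that visit. State when follow-up ends.
2. Report by period the proportion of patients tested, tests per patient, and positives per patient tested.
3. Add an estimate limited to tested follow-up, preferably interval-censored between negative and positive test dates.
4. State that simple Kaplan-Meier censoring at the last test can mildly overcorrect in the video's favour, and that tested patients are a selected group whose selection the video may itself change.
5. State that a period difference in STDs will not be interpreted for Hypothesis 5 without the testing rates beside it.

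The cost is wording and modest extra analysis, since STD results and test dates are already collected. The companion estimate has a smaller and selected denominator, so it will be less precise for an outcome that is already unpowered.

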***Information management and analysis software:***

The data manager will use SAS and SPSS to manage and clean the patient medical data and Excel to manage and clean the observational data. The data manager will mail the cleaned data to CDC on an encrypted USB drive. CDC will use SAS and SPSS to analyze the patient medical data and EZ-Text and Excel to analyze the observational data.

***Bias in data collection, measurement, and analysis:***

Biases with regard to the observation: Observation bias could affect the validity of the data. This bias will be minimized by having only one observer and training him to conduct the observation in a systematic fashion using an online instrument to guide the data collection, which will enhance observer consistency. Bias is also minimized by the data collection instrument requiring a low level of observer inference or interpretation of observed behaviors. In a waiting room patients are a collection of individuals and not participants in an interactive group, so the presence of a non-interacting observer should not influence patient behavior. Bias from expectancy effects will be offset by checking for correspondence between observed disengagement and medical outcomes addressed during segments when many patients were disengaged. There could be bias due to an inability of the observer to correctly recognize the HIV-positive patient characteristics (race/ethnicity, age, gender) or whether or not patients are truly engaged with the video or merely looking in the direction of the video screen. To a certain extent, this bias is inherent in the study design, and would be difficult to avoid without approaching the patients. Measurement bias could affect the generalizability of the data. Observations are limited to once per facility. Bias is minimized by conducting observations for eight hours, for a total of 24 assessments and an estimated 192 to 336 patients observed across all three facilities. The eight-hour observation period will minimize time-of-day bias but will be affected by day-of-week and month-of-year differences. Observations will be conducted during the first two months of the intervention period to minimize potential bias from previous exposure to the video.

Biases with regard to the patient medical data:

Bias is inherent in the study because the 10-month data collection timeframe is less than the 12 months required by core indicators for the outcomes being evaluated. Patient populations among the facilities are heterogeneous, so combining their medical data cannot be done reliably. Bias can occur from loss to follow-up (i.e., failure to return to the clinic) in either beta-test period. This attrition will be adjusted for analytically. Use of historical comparison will tend to exaggerate treatment effect as patients in this group benefit from amount of health care over time. Bias also can result from differences in individual medical care providers recording medical tests performed and treatment regimens prescribed and not performing medical tests at each clinic visit. Bias also can result from providers not testing all potentially infected anatomical sites for STDs. Bias may be introduced if there is a change in treatment guidelines during the 20-month data collection period.

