***Intervention or treatment:***

The intervention that will be tested will be a short “soap opera” style waiting room video with three interwoven vignettes that incorporate key prevention messages aimed at increasing early treatment initiation, treatment adherence, retention in care, and partner protection for people with HIV. The video will contain characters who represent various populations, including women, gay men, heterosexuals, African-Americans, and Latinos. The video will also include a short animation focusing on treatment adherence. The video is meant to play in the waiting room throughout the day for 10 months. Optimally, the video will play on a continuous loop. Some facilities may need short pauses between video replays based on their local circumstances. If this need arises, the pause interval will be discussed with and approved by CDC.

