***D. DATA HANDLING AND ANALYSIS***

***Data collection:***

Observational data: A detailed observation protocol is outlined in Appendix 2: Observation Protocol.

Patient medical data: De-identified patient medical data will be supplied by the facilities. The data will consist of data that each facility is already collecting in their EMR. The data will be de-identified by staff at each facility before being placed on an encrypted USB drive.

***Data entry, editing and management, including handling of data collection forms, different versions of data, and data storage and disposition:***

Observational data will be entered into Survey Monkey (a commercially available online survey solutions service) by the observer during the 8 hours of systematic observation at each beta-test facility. We will use the SSL encryption feature on Survey Monkey, which ensures the security of the data as it moves between the tablet computer and Survey Monkey servers, and during downloading of the data. Survey Monkey uses Verisign certificate Version 3, 128 bit encryption. The data will be stored in the Survey Monkey database until the end of the study. The observational data will not contain any information that could identify any of the patients in the waiting room (See Appendix 3: Observation Instrument). The Beta-Test Manager will be responsible for downloading the data from Survey Monkey in Excel format. He will clean the data, place it on an encrypted USB drive, and mail it to the CDC for analysis. The PI will destroy the observational dataset at the end of the project after CDC has confirmed receipt and approval of the data.

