***Data analysis plan, including statistical methodology and planned tables and figures:***

Analysis of observational data: Patient engagement with the video during the first half of each assessment (i.e., all waiting room patients) will be analyzed qualitatively and separately for each of the six video segments (i.e., opening, three stories, and two animations). Codebooks for the content analyses will be developed after the data are received. Content analyses of the observations will look for number of patients who watch or ignore the segment and if the segment elicits any positive or negative responses. Relationships will be sought between frequency of disengagement (i.e., number of patients who ignored or exhibited a negative reaction during a segment) and characteristics of the disengaged patients (i.e., apparent age, gender, race/ethnicity). Patient engagement during the second half of each assessment (i.e., four select patients) will be analyzed the same way; however, analysis will attempt to identify within segments the scenes that are associated with patient disengagement. In addition, data from the second half of the assessments will be evaluated quantitatively for estimated duration of engagement with each segment. Patterns of disengagement across the three facilities will be sought. We will use EZ-Text qualitative software to assist with our qualitative data analysis.

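### The outcome check in Protocol III.D cannot offset observer expectancy bias: it examines only segments recorded as disengaging and compares them with clinic-wide outcomes not linked to the people observed

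*Protocol*

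**What the plan says.** The bias discussion in Protocol III.D names several protections for the observation: one trained observer, a structured online instrument and little need for observer interpretation. For expectancy it makes a specific claim: "Bias from expectancy effects will be offset by checking for correspondence between observed disengagement and medical outcomes". The sentence goes on to limit the outcomes to those covered in particular segments: "medical outcomes addressed during segments when many patients were disengaged".

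The data analysis plan in III.D defines disengagement from the observer's own record, as the "number of patients who ignored or exhibited a negative reaction during a segment". Hypothesis 1 has a direction: "Exposure to the video will elicit favorable reactions from patients".

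The two data sources are separate. On the observation, the data management text in III.D says: "The observational data will not contain any information that could identify any of the patients in the waiting room". On the medical records, III.B (Sampling) says: "The sample for the patient medical record data will include all HIV-positive clinic patients and their records". The Limitations section concedes that actual exposure to the video cannot be measured.

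The General approach paragraph under Hypotheses gives both sources the same task: "Both the observation and the review of de-identified patient medical data are meant to identify areas of the video that need to be refined".

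**The concern.** The protocol claims that a bias is corrected, and the claim depends on a check with two structural weaknesses. First, the observer's own record decides which segments are checked. Second, what they are checked against is a before/after comparison of whole clinic populations, which contains nothing about the people watched on the observation day.

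Hypothesis 1 and Objective 1 rest on one observer, who knows that the video is under test. If the offset claim stands, a reader may take the ratings as corrected for the observer's expectations when nothing in the design corrects them. The General approach paragraph extends the problem by implying that clinic-wide outcomes can show which parts of the video need work.

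**Working it through.** **1. The plan's own figures.** The bias check has no stated figure. The outcome comparisons it would draw on do (III.B, Sampling: two-sided 5%, 80% power, Fisher's exact test). With d = p2 − p1 and p̄ the mean of the two proportions:

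n = [1.96·√(2p̄q̄) + 0.842·√(p1q1 + p2q2)]² / d²

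For 70% against 77%: (1.223 + 0.524)² / 0.07² ≈ 623. The continuity correction, which approximates Fisher's test, is n′ = (n/4)·[1 + √(1 + 4/(n·d))]² and gives 652, against 650 stated. For 75% against 82% it gives 568 (566 stated), and for 50% against 60% it gives 408 (407 stated). The figures reproduce and can serve as inputs.

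**2. What enters the check.**

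| Segment in truth | Recorded as | Enters the check? |
|---|---|---|
| Engaging | Engaging | No |
| Disengaging | Engaging (attention over-recorded) | No |
| Engaging | Disengaging | Yes |
| Disengaging | Disengaging | Yes |

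Rows two and three are the possible errors. The check can reach only row three. Row two, the error that favours Hypothesis 1, takes the segment out of the check.

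**3. What the outcomes can say about a rating.** III.B expects 192 to 336 people observed and 2,000 to 4,000 patients in the records. The observed are therefore between 192/4,000 = 4.8% and 336/2,000 = 16.8% of that number. Some may not be in the records at all, since III.B says companions cannot be told apart from patients. There are no identifiers to link the rest and no exposure measure. The outcome result is fixed by the clinic population's records over two 10-month periods, and the accuracy of a one-day rating does not enter it.

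**4. Illustration.** The protocol does not define correspondence, so two rules are assumed, for one flagged segment and one outcome.

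*Rule A: the outcome does not improve significantly.*
- No video effect and no time trend: 1 − 0.05/2 = 97.5%.
- Planned effect at 80% power: 1 − 0.80 = 20%.
- No video effect but an assumed upward trend d from 70%: 1 − Φ{[d − 1.96·√(2p̄q̄/n)] / √[(p1q1 + p2q2)/n]} (normal approximation).

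Example with n = 650 and d = 0.02: (0.02 − 0.0493)/0.0252 ≈ −1.17, Φ ≈ 0.122, so 88%.

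| n per period | No trend | +2 points | +3 points | +5 points |
|---|---|---|---|---|
| 650 | 97.5% | 88% | 78% | 48% |
| 1157 | 97.5% | 82% | 64% | 23% |
| 2000 | 97.5% | 71% | 44% | 6% |

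The values 650 and 1157 are the protocol's sizes before and after attrition. The value 2000 assumes the lower end of the total patient estimate in each period. The trends are assumptions; the protocol gives no size.

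*Rule B: the outcome does not improve numerically.* About 50% without trend. At 650 per period, with trends of 2, 3 and 5 points: 21.3%, 11.5% and 2.2%.

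The answer moves with the rule, the trend and the sample size. None of the expressions contains a term for observer accuracy.

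**The case against.** **The terms are undefined, and the definition may sit in an analysis plan not shown.** This stands. The missing definition is no finding, and no single probability belongs to the protocol. A reader might infer from the 97.5% that the check would almost always find correspondence when the video does nothing. The documents do not support that. The figure needs an assumed rule and no time trend, while III.D itself expects the historical comparison to exaggerate the effect. Moreover, where a dull segment sits beside an unimproved outcome, the match describes the facts correctly and is not a false alarm.

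**Segments can be matched to outcomes by content.** This stands in part. A reader might infer that no outcome belongs to any one segment, but III.C describes a short animation focused on adherence. The same section also describes "three interwoven vignettes that incorporate key prevention messages aimed at increasing early treatment initiation, treatment adherence, retention in care, and partner protection", so adherence is not confined to that animation. In either case a topic match does not test a rating.

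**The contrast between 97.5% and 20% looks informative.** It would be so only if disengagement on one day at each site determined whether one segment moved one clinic-wide outcome over 10 months. The protocol cannot establish that: it has no exposure measure, and it says the data will not show conclusively that outcomes are due to the video.

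**Expectancy could run the other way.** The observer is sent to find points needing refinement and may over-record disengagement, which does enter the check. This stands as to direction, but the outcomes are no better a test of that error.

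**Other safeguards and limitations are stated.** Training and a structured instrument promote consistency, and a consistent expectation passes through both. The Limitations section admits uncertainty about whether patients are truly engaged, but it does not name expectancy bias.

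**The harm is limited.** This stands. A reader might infer that segments will be re-edited on chance matches with outcomes. III.A bases refinement on the observation itself, and no section makes editing depend on the match.

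**Conclusion.** The point holds as a false claim of bias control. As described, the check cannot offset expectancy bias, because it never examines over-recorded engagement in unflagged segments, and its comparator carries no information on observer accuracy under any definition of correspondence. Both conclusions follow from the protocol's text and need no probability model. The range of 6% to 97.5% under Rule A, and about 50% under Rule B without trend, is illustration and depends on the assumed rules and trends.

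The reach is limited to what may be concluded for Hypothesis 1 and to the basis for refining the video. The medical outcome analyses do not use the observation data, so a reader should not infer any fault in Hypotheses 2 to 5 from this point.

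**What to change.** - **III.D, Bias in data collection, measurement, and analysis:** delete the statement that expectancy bias will be offset by this check, and do not use agreement between segments and outcomes to support the accuracy of the ratings.
- **III.D, Limitations of study:** list expectancy bias of the single, unblinded observer as an uncorrected limitation of Hypothesis 1.
- **General approach, under Hypotheses:** state that segment-level refinement rests on the observation data and that the medical data assess the video as a whole.

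These are wording changes in three places and need no new data, patients or staff. The downside is that the stated control of observer bias becomes less favourable.
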